#### Exclusion criteria

Patients who meet any of the following criteria will be excluded from this study.

Patients with serious internal diseases, tumors and other malignant diseases, infectious diseases, and mental illnesses.Contraindications for electrical stimulation devices: such as with pacemakers or other implantable devices; history of epilepsy or/and seizures; history of head trauma or head and spinal cord surgery; bleeding disorders; in pregnancy or lactation or planning to become pregnant in the next 6 months; injuries, swelling, or scarring at the skin of the stimulating sites; sensory disturbance or allergy to electrical stimulation.Have taken muscle relaxant drugs in the past month or have received botulinum toxin injections in a spastic limb within the past 6 months.Have received transcranial direct current stimulation, transcutaneous electrical stimulation or acupuncture in the past 6 months.

#### Withdrawal criteria

Following patients will be withdrawn from the study:

Those who undergo serious adverse events.Those with deterioration of disease or have a serious complication during the study.Those who withdraw informed consent for any reason.

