### Outcome measurement

#### Primary outcome

The primary outcome will be the change from baseline in muscle tone assessed with MAS in elbow, wrist, knee, and ankle 4 weeks after baseline (the end of the intervention). The detailed scoring rules of MAS with 6-level (level 0, 1, 1+, 2, 3, 4) are consistent with previous study (41). In the analysis of MAS scores, a derived MAS score with a 6-point scale from 0 to 5 (level 0, 1 equivalent to 0 and 1 respectively, level 1+ transformed into 2, 2 into 3, 3 into 4, and 4 into 5) will be used for practicality. To ensure the objectivity and accuracy of the MAS assessment, the independent evaluator will be instructed via specific training to use a medium velocity of passive movements, lasting about 1 s (42). Subsequently, MAS will be measured for above mentioned four joints with different levels in each joint, and then the sum of MAS scores in four joints will be recorded as the total MAS score.

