### Safety evaluation

The investigators and operators will closely monitor the patients during the 4-week treatment period. If the patient feels any discomfort, the intervention will be stopped immediately, and the patient’s condition will be treated appropriately. Any adverse reaction caused by electrical stimulation, such as localized redness, swelling, pain, or other adverse events, will be recorded by operators.

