### Statistical analysis

Statistical analyses will be performed by statisticians who are independent of the research team and have no knowledge of the study groupings or study settings. Statistical analyses will be performed using IBM SPSS Statistics 25.0 software and follow intention-to-treat (ITT) principles to ensure all subjects are included after randomization. Missing data will be handled by multiple imputations. Continuous variables that follow a normal distribution are presented as mean ± standard deviation, and those that do not follow a normal distribution are given as median and interquartile range. Comparisons within groups will be performed via paired t-tests, and difference among groups will be analyzed by the one-way ANOVA test. For measurements at different time points, differences were assessed using repeated-measures ANOVA followed by Bonferroni *post hoc* tests. The test level is 0.05, with *p* < 0.05 indicating a statistically significant difference.

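### Withdrawing patients from the study, rather than only from stimulation, after a serious event or deterioration loses their later outcomes by rule; this weakens the intention-to-treat analysis, and imputation may not fully repair it

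*Protocol article*

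**What the plan says.** The Withdrawal criteria (under Participants) begin "Following patients will be withdrawn from the study" and list three grounds: "Those who undergo serious adverse events"; "Those with deterioration of disease or have a serious complication during the study"; and "Those who withdraw informed consent for any reason". The first two are events after randomisation that signal a bad course. The third is the patient's own decision. All three have the same consequence.

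Stopping treatment is handled elsewhere. Under Safety evaluation, if a patient feels discomfort, "the intervention will be stopped immediately", and leaving the study is not mentioned.

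The Statistical analysis section says the analyses will "follow intention-to-treat (ITT) principles to ensure all subjects are included after randomization" and that "Missing data will be handled by multiple imputations". The imputation model and its assumption are not described.

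The primary outcome is the change in total MAS from baseline to week 4. Table 1 schedules MAS at weeks 0, 1, 2, 3, 4 and 8. The other efficacy outcomes are scheduled at baseline and week 4, and adverse events at weeks 1 to 4.

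**The concern.** The article distinguishes ending the intervention from ending participation, and for these patients it chooses the latter. No section says that outcomes are still assessed after withdrawal. The primary week-4 value and the week-8 MAS are therefore missing by rule for anyone meeting the first two grounds before those visits, and the reason for missingness may be related to the value that was not seen.

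Intention-to-treat needs two things: analysing everyone as randomised, and following everyone up. The Statistical analysis section secures the first. The withdrawal rule gives up the second for the patients in whom it matters most. Imputation then has to stand in for data that could have been collected.

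What is at stake is an overstated mean improvement in any arm with such withdrawals, and a biased contrast if arms differ in how often they occur or how severe they are. Arms could differ: only two receive stimulation, control patients know their allocation, and the article gives no threshold for deterioration. This is a rule about data collection, so no analysis plan can recover the values later.

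**Working it through.** **Yardsticks from the plan.** The Sample size section assumes MAS decreases of 1, 0.75 and 0.45 with SD 0.52. The pairwise differences are 1 − 0.75 = 0.25, 0.75 − 0.45 = 0.30 and 1 − 0.45 = 0.55. The stated size reproduces: a three-group one-way ANOVA at α = 0.05 has power 0.892 with 23 per group and 0.905 with 24, so 24 is the minimum for 90%, and 24 / (1 − 0.20) = 30. The sample size is not in dispute.

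**Quantities the article does not give (assumed).**
- w: share of an arm withdrawn on the first two grounds.
- g: how much smaller the true mean MAS decrease is in those patients than in the rest.
- s: share of that shortfall already visible in MAS before withdrawal.
- b: slope of the week-4 decrease on the week-3 decrease among patients not withdrawn, taken as 0.8.

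**Step 1: earlier MAS shows nothing of the deterioration (s = 0).** Imputed values centre on the mean of the patients not withdrawn, so the arm's mean decrease is overstated by w × g:

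| Withdrawn | g = 0.5 | g = 1.0 | g = 2.0 |
|---|---|---|---|
| 1 of 30 | 0.02 | 0.03 | 0.07 |
| 3 of 30 | 0.05 | 0.10 | 0.20 |
| 6 of 30 | 0.10 | 0.20 | 0.40 |

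The last row is an extreme. It would use up the whole 20% dropout allowance, which covers every cause.

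**Step 2: imputation uses the week-3 MAS.** The imputed mean for a withdrawn patient falls by b × s × g, which leaves a bias of w × g × (1 − b × s). With w = 0.10 and g = 1, and a mean decrease of 1.00 in the rest, the true arm mean is 1.00 − 0.10 × 1 = 0.90. The imputed arm means are:
- s = 0: 1.00, bias 0.10 × (1 − 0) = 0.10.
- s = 0.5: 0.96, bias 0.10 × (1 − 0.4) = 0.06.
- s = 1: 0.92, bias 0.10 × (1 − 0.8) = 0.02.

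A simulation of regression imputation with 400,000 patients gave the same three means to two decimals. Even when week 3 shows the whole shortfall, some bias remains, because the slope is below 1.

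**Step 3: between arms.** The bias in a contrast is the difference of the two arms' biases. If w, g and s are equal it is zero. If only one arm is affected, the Step 2 range of 0.02 to 0.10 is 8% to 40% of 0.25, 7% to 33% of 0.30 and 4% to 18% of 0.55.

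**Step 4: with follow-up.** If week-4 MAS is collected after the event and analysed, nothing is imputed for these patients and this bias is zero.

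**The case against.** The strongest reply is that nobody leaves the analysis. All randomised patients are included, values before withdrawal are kept, and the weekly MAS gives the imputation something to work with. That much stands, and it rules out three stronger readings.

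- A reader might infer that the worst outcomes are deleted. Only data after withdrawal are lost, and deterioration of disease is not defined as a worse MAS. That withdrawn patients have a poorer MAS change is plausible but assumed, in direction as well as size.
- A reader might infer a flat contradiction with intention-to-treat. The stated rule, that all subjects are included, is formally met by imputation. The conflict is with the principle of following everyone.
- A reader might infer that missing values are filled in from patients who did well. They would be modelled on patients who were not withdrawn, some of whom may not have improved, and the model is not stated.

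It is also fair to say that such events may be rare. Patients must be in a stable state and walk 10 metres unaided, serious internal disease is excluded, and treatment lasts 4 weeks. A bias of 0.10 is below one standard error of a pairwise difference at the planning SD, 0.52 × √(2/30) = 0.134. The trial calls itself a pilot. Loss of safety follow-up is an inference: the qualifying event precedes withdrawal, and Table 1 schedules no adverse-event recording at week 8 for anyone. A missing-data sensitivity analysis is commonly left to the analysis plan, so its absence here is no fault.

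None of this answers the remaining point. The withdrawal rule, followed as written, stops outcome collection where it could continue, and imputation is a weaker substitute.

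**Conclusion.** The concern holds in this limited form. Two of the three withdrawal grounds end study participation because of a bad course, and nothing in the article preserves outcome assessment afterwards. Missingness may then depend on the outcome and on the arm. Imputation assuming missing at random may reduce the bias but cannot be relied on to remove it.

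The size is unknown. With 10% of an arm withdrawn and a true change 1 point worse, that arm's mean decrease is overstated by about 0.02 to 0.10, depending on how much the earlier MAS shows. These inputs, and the 0.8 slope, are assumptions. The effect on a between-arm comparison is near zero if such events are few, or if their frequency and severity are balanced. A reader might take the 20% dropout allowance as the share withdrawn for these reasons, or suppose a large imbalance between the 20 Hz and 100 Hz arms. The article supports neither. The case for change rests on the rule being avoidable and the lost data unrecoverable, not on a demonstrated large bias.

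**What to change.** Reconcile the Withdrawal criteria with the Statistical analysis section by separating the end of stimulation from the end of outcome assessment. State that, unless consent to follow-up is withdrawn, every randomised patient keeps the scheduled week-4 and week-8 MAS assessments, the other week-4 outcomes where feasible, and adverse-event recording, and is analysed in the group assigned. No change to when stimulation is stopped is proposed.

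As an optional addition, values still missing after such an event could be covered by a sensitivity analysis that sets the imputed change to no improvement or shifts it by a fixed amount.

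The cost is a wording change and a few extra assessments at visits already scheduled. Some may not be feasible in very ill patients, so some missing values will remain. The change should be made before any such patient is withdrawn, because values not collected cannot be recovered.

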### Randomization and blinding

Eligible participants will be randomly assigned to 3 groups in a ratio of 1:1:1 by an independent statistician using a randomization sequence generated with SPSS 25.0 and will be concealed from the investigators. The random number of patients meeting criteria will be telephoned by the unaffiliated investigator. Due to the characteristics of interventions, participants in the standard care control group will be aware of their allocation ineluctably.

An independent researcher will pre-set the frequency of the Acu-TENS and then cover the frequency display site to ensure the operators remain blinded to the allocation (different frequencies of Acu-TENS) throughout the study. To reduce the risk of bias, the evaluators and statisticians will be blinded to group allocation during outcome assessment and data analysis.

### Intervention

Throughout the trial, all participants will receive standard care in modern medicine for ischemic stroke, corresponding symptomatic or supportive treatment, and regular rehabilitation treatment as well. Simultaneously, Acu-TENS combined with tDCS will be additionally applied to the participants in 2 observational groups. In this study, the acupuncture meridian points used for Acu-TENS and the stimulation locations of International Standard Scalp Acupuncture used for tDCS are referenced from the standards determined by the World Health Organization (38, 39). The locations of the acupoints used in this trial and the methods of electrodes connection are illustrated in Figure 2, while the detailed locations of acupoints are shown in Table 2. All acupoints-based treatment will be conducted independently by the same two acupuncturists, who have at least 5 years of work experience and to be trained specifically in a standard process prior to the study.

**Figure 2 fig2:**
[figure not shown]
Interventions and locations of acupoint (right head injury and left limbs affected as an example). tDCS, transcranial direct current stimulation; Acu-TENS, acupoints-based transcutaneous electrical nerve stimulation; MS 6, anterior oblique line of vertex-temporal; LI 11, Quchi; TE 5, Waiguan; GB 34, Yanglingquan; ST 37, Shangjuxu. Four acupoints figures of LI 11, TE 5, GB 34, and ST 37 cited from WHO (37, 38). Figure was created on Biorender with permission to publish.

**Table 2 tab2:** Locations of acupoints [WHO (37, 38)].

**Acupoints**	**Side**	**Locations**
Quchi (LI 11)	Affected limbs side	On the lateral aspect of the elbow, at the midpoint of the line connecting the depression lateral to the biceps brachii tendon with the lateral epicondyle of the humerus.
Waiguan (TE 5)	Affected limbs side	On the posterior aspect of the forearm, midpoint of the interosseous space between the radius and the ulna, 2 *cun* proximal to the dorsal wrist crease.
Yanglingquan (GB 34)	Affected limbs side	On the fibular aspect of the leg, in the depression anterior and distal to the head of the fibula.
Shangjuxu (ST 37)	Affected limbs side	On the anterior aspect of the leg, 6 *cun* inferior to the lateral depression to the patellar ligament of the knee.
Anterior Oblique Line of Vertex-Temporal (MS 6)	the injured side of head (Opposite to the affected limbs)	From the Qianshencong (EX-HN1, at the vertex of the head, 1 *cun* anterior to Baihui GV20) oblique to the Xuanli (GB6).

Cun: a unit used to locate acupuncture points.

#### Observational groups

Patients will receive Acu-TENS at 20 Hz or 100 Hz combined with the same tDCS treatment. The intervention will last for 12 sessions, each 20 min for tDCS and 30 min for Acu-TENS, 3 times a week for 4 weeks. Treatment will be performed using a transcranial electrical stimulator [NeuStim NSS10E, Neuracle Technology (Changzhou) Co., Ltd., Changzhou, China] and a transcutaneous electrical nerve stimulator (QL/T-IIA, Sichuan Qianli Beoka Medical Technology Co., Ltd., Chengdu, China).

The NeuStim NSS10E transcranial electrical stimulator has two output channels, one of which is used to connect a pair of rectangular electrodes (Anode 50 × 100 mm, Cathode 50 × 50 mm). The patient will be placed in a comfortable supine position to fully expose the acupoints on the head and affected limbs. After skin cleaning, the anode will be placed on the upper 3/5 of the Anterior Oblique Line of Vertex-Temporal (MS 6) of scalp acupuncture on the injured side, and the cathode will be placed on the supraorbital region on the contralateral side. The tDCS will applied for 20 min at a current intensity of 1 mA (29, 40).

The QL/T-IIA transcutaneous electrical nerve stimulator has 2 output channels, each connected to a pair of electrodes (40 mm × 40 mm). After skin cleaning, each pair of electrodes will be attached at two acupoints on the affected limbs respectively, Quchi (LI 11) and Waiguan (TE 5) on the upper limb, while Yanglingquan (GB 34) and Shangjuxu (ST 37) on the lower limb in a square wave with a pulse width of 0.2 ms. The frequency will be set to either 20 or 100 Hz depending on the grouping of patients. The stimulation intensity of each output will be adjusted to 2–3 times of the sensory threshold of each participant without eliciting a muscle contraction. The Acu-TENS will last for 30 min.

#### Standard care control group

Participants assigned to the standard care control group will only receive standard management according to the guidelines in modern medicine for ischemic stroke, including symptomatic or supportive treatment, and regular rehabilitation treatment individually, without Acu-TENS or tDCS.

### Outcome measurement

#### Primary outcome

The primary outcome will be the change from baseline in muscle tone assessed with MAS in elbow, wrist, knee, and ankle 4 weeks after baseline (the end of the intervention). The detailed scoring rules of MAS with 6-level (level 0, 1, 1+, 2, 3, 4) are consistent with previous study (41). In the analysis of MAS scores, a derived MAS score with a 6-point scale from 0 to 5 (level 0, 1 equivalent to 0 and 1 respectively, level 1+ transformed into 2, 2 into 3, 3 into 4, and 4 into 5) will be used for practicality. To ensure the objectivity and accuracy of the MAS assessment, the independent evaluator will be instructed via specific training to use a medium velocity of passive movements, lasting about 1 s (42). Subsequently, MAS will be measured for above mentioned four joints with different levels in each joint, and then the sum of MAS scores in four joints will be recorded as the total MAS score.

#### Secondary outcomes

Secondary outcomes will involve changes in surface electromyography (SEMG) of the lower arm and calf muscles on the hemiplegia side, Fugl-Meyer Motor Function Scale, Modified Barthel Index (MBI), and 10-meter walk test among the three groups at different time-points. Assessment of all secondary outcomes will be performed at baseline and at the end of the treatment (week 4).

SEMG can reflect the myoelectric activity of muscles. In this trial, the SEMG results of the flexor carpi radialis muscle, extensor carpi radialis longus muscle, gastrocnemius muscle, and tibialis anterior muscle will be evaluated by an EMG acquisition system [NSW304M, Neuracle Technology (Changzhou) Co., Ltd., Changzhou, China] at baseline and week 4. The myoelectric electrodes will be affixed regarding the procedure recommended by the European Commission (43), using round Ag/AgCl electrode sheets with a diameter of 10 mm, 20 mm apart to the middle of the muscle belly, as shown in Figure 3. The patient will be asked to relax and be quiet for at least 3 min before the assessment. After starting the recording, the EMG of the patient’s quiet state will be first collected for 3 min, and then the patient’s wrist or ankle joint will be rapidly flexed and extended 3 times, with an interval of 1 min each time. The maximum value of 3 repetitions will be taken as the integrated EMG (iEMG) value. The data will be analyzed from the recordings, including iEMG and co-contraction ratio (CR). The CR value can be calculated according to this formula:

CR (%) = iEMG value of antagonistic muscle/(iEMG value of agonistic muscle+ iEMG value of antagonistic muscle) × 100%.

The Fugl–Meyer Motor Function Scale is a 100-point scale consisting of 66 points for the upper extremities and 34 points for the lower extremities, and is a commonly used scale for assessing patients’ motor function (44). The MBI is also a 100-point scale that evaluates the degree of assistance needed for activities of daily living (45). The 10-meter walk test can assess the patient’s lower limb movement. Patients will be advised to complete both questionnaires and the walk test at baseline and week 4. Figure 3 demonstrates the method of above assessments.

**Figure 3 fig3:**
[figure not shown]
Evaluations and outcomes (left limbs affected as an example). MAS, modified Ashworth scale; SEMG, surface electromyography; iEMG, integrated EMG; CR, co-contraction ratio; MBI, Modified Barthel Index. Figure was created on Biorender with permission to publish.

### Safety evaluation

The investigators and operators will closely monitor the patients during the 4-week treatment period. If the patient feels any discomfort, the intervention will be stopped immediately, and the patient’s condition will be treated appropriately. Any adverse reaction caused by electrical stimulation, such as localized redness, swelling, pain, or other adverse events, will be recorded by operators.

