**Methods:**

A total of 90 post-ischemic stroke patients with spastic hemiplegia will be intervened for 4 weeks and followed up for 4 weeks. They will be randomly assigned to three groups including two observation groups and a standard care control group in a 1:1:1 ratio. All patients will receive standard care and regular rehabilitation accordingly. In addition, the two observation groups will receive 12 sessions of Acu-TENS at 20 Hz or 100 Hz for 30 min combined with 1 mA tDCS for 20 min, three times a week, for 4 weeks. The primary outcome is the change in total modified Ashworth scale (MAS) score from baseline to week 4. Secondary outcomes include changes in surface electromyography (SEMG), Fugl-Meyer Motor Function Scale, Modified Barthel Index (MBI), and 10-meter walk test from baseline to week 4. MAS score will also be measured after 4 weeks of follow-up. Adverse events throughout the study will be recorded.

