**Evaluations**							
MAS		**×**	**×**	**×**	**×**	**×**	**×**
SEMG		**×**				**×**	
Fugl–Meyer motor function scale		**×**				**×**	
MBI		**×**				**×**	
10-meter walk test		**×**				**×**	
**Adverse events**			**×**	**×**	**×**	**×**	

The intervention will last for 12 sessions, three times a week for 4 weeks. MAS, modified Ashworth scale; SEMG, surface electromyography; MBI, Modified Barthel Index.

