### Data management

The data required for the study of all patients will be recorded on the printed case report forms (CRFs), including observation time points, outcome measures, adverse reactions, and safety evaluations. The private information of each participant, including name, phone number and other identity will be protected from disclosure. An independent data manager will check the accuracy and timeliness of the data and keep all data safe. No artificial data modification will be allowed after the end of the trial.

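### Adverse events are promised for the whole study but scheduled only in weeks 1 to 4, and the named recorders may not cover the control arm evenly

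*Protocol article*

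**What the plan says.** The Methods paragraph of the abstract says that patients "will be intervened for 4 weeks and followed up for 4 weeks" and that "Adverse events throughout the study will be recorded".

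The Safety evaluation section says: "The investigators and operators will closely monitor the patients during the 4-week treatment period". It then covers reactions caused by the electrical stimulation, gives local examples, and ends: "or other adverse events, will be recorded by operators".

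In Table 1 the row "Adverse events" is marked in weeks 1, 2, 3 and 4 and is blank at week 8. The MAS row is marked at week 0, weeks 1 to 4 and week 8.

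Randomization and blinding describes pre-setting the device and covering its display "to ensure the operators remain blinded to the allocation (different frequencies of Acu-TENS) throughout the study". The Intervention section gives all acupoint-based treatment to the same two acupuncturists. Control patients receive standard management and "regular rehabilitation treatment individually, without Acu-TENS or tDCS".

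**The concern.** The article gives two different windows for adverse events. Staff working from the schedule and the Safety evaluation section would stop collecting at week 4. A reader of the abstract would take the reported events to cover 8 weeks. Safety is one of the aims in the Introduction, and the abstract's Discussion presents the combination as evaluated for the first time. Events arising in weeks 5 to 8 are not scheduled for collection in any arm, so a low count could partly reflect the shorter window.

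The second issue is who does the recording. All-cause events also occur under standard care. If the people who record them are mainly in contact with stimulated patients, those events may be captured more fully in the stimulated arms, and an apparent excess over control could be due to ascertainment.

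**Working it through.** The plan gives no safety figure to reproduce, so the check compares the passages and counts weeks and contacts.

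**Window**

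1. Time on study per patient (abstract, Methods): 4 weeks of treatment + 4 weeks of follow-up = 8 weeks.
2. Weeks with an adverse-event mark (Table 1): weeks 1, 2, 3 and 4 = 4 weeks.
3. Scheduled coverage: 4 / 8 = 50%. Not scheduled: 8 − 4 = 4 weeks, namely weeks 5 to 8.
4. An existing contact in the gap: the MAS row is marked at week 8, so an assessment already takes place at which the question could be asked.

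| Place | Window for adverse events |
|---|---|
| Abstract, Methods | Whole study, so to week 8 |
| Table 1 | Weeks 1 to 4 |
| Safety evaluation | 4-week treatment period |

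The two operational places agree with each other and conflict with the abstract. A single missing cell in Table 1 would not explain this, because the Safety evaluation text independently gives the shorter window.

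**Recorder**

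1. The recording sentence in Safety evaluation names operators and nobody else.
2. Operators are kept blind to the Acu-TENS frequency by a covered display, which points to people who handle the stimulator. The Intervention section assigns the acupoint-based treatment to two acupuncturists. Controls receive neither stimulation. Together these suggest that operators are the treating staff of the stimulated arms. No passage says so outright.
3. Planned stimulation sessions per stimulated patient (Observational groups): 3 per week × 4 weeks = 12.
4. Planned MAS assessments common to all three arms after baseline (Table 1): weeks 1 to 4 and week 8, so 4 + 1 = 5.
5. Stimulated patients therefore have 12 treatment sessions in addition to the 5 assessments that every patient has. If events are noted at treatment sessions, there are more occasions to note them in the stimulated arms.
6. Both stimulated arms have the same session count, the same two acupuncturists and operators blind to frequency. Ascertainment between 20 Hz and 100 Hz is therefore even by design.

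The documents give no adverse-event rate and no rate of capture by arm, so the size of any bias against control cannot be calculated from them.

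**The case against.** **Detail left to a fuller protocol.** An article need not name who records events in every arm. This stands for the recorder, and is why that part is put as a risk. It does not answer the window, which the article itself states in two incompatible ways.

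**Half the calendar is not half the safety information.** Stimulation ends at week 4, and the reactions given as examples are local. This stands: 50% describes scheduled weeks, and no share of events is implied. The text nevertheless includes other adverse events, and the abstract promises the longer period.

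**Controls are not outside the safety system.** The Safety evaluation section has investigators as well as operators monitoring patients, without limiting this to an arm. The adverse-event row in Table 1 is not split by arm. Data management puts data for all patients on case report forms that include adverse reactions and safety evaluations. Quality control adds ethics committee review of safety. A reader might infer that safety cannot be compared between arms at all; these passages rule that out. They still do not say who asks control patients, or when, and review can only cover what was collected.

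**Operators and controls.** A reader might infer that operators have no contact with controls. That is a reasonable inference but not a stated fact, and all arms share the scheduled MAS assessments. The recording sentence also opens with stimulation reactions and may be meant to give operators only those. In that case no recorder is named for other events in any arm.

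**Serious events might surface anyway.** The withdrawal criteria refer to serious complications during the study. That is a rule for withdrawal and sets no collection schedule.

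**Precision.** A reader might support the point with an upper confidence limit for zero observed events. That limit depends on the number of patients and is the same for 4 or 8 weeks of observation, so it says nothing about the missing window.

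**Conclusion.** The contradiction over the window is established by the text alone. The abstract covers 8 weeks, while Table 1 and Safety evaluation cover 4, so weeks 5 to 8 have no scheduled adverse-event collection despite an existing week 8 assessment.

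The arm comparison supports a narrower conclusion. Comparison of all-cause events between stimulation and standard care is at risk of unequal ascertainment. This rests on the inference that operators are the staff delivering stimulation, and its size is unknown. The comparison of 20 Hz with 100 Hz is not affected.

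The change should be made, because safety is a stated aim and the correction is small.

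**What to change.** - Add an adverse-event mark at week 8 in Table 1, and extend the period in Safety evaluation so that both match the abstract.
- Have the investigators ask the same adverse-event question in all three arms at each existing weekly MAS visit and at week 8. The blinded MAS evaluator should not ask it, since answers about skin reactions could reveal the allocation.
- State in Safety evaluation that operators record the stimulation reactions they observe, and report these separately for the two stimulated arms. Base the comparison with standard care on the common question.

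The cost is one table cell, one case-report-form item and a few minutes per existing visit. No extra visits or staff are needed.
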